### 6.2 Sample size including power calculation

The sample size calculation is based on the difference in change in the primary outcome (physical activity) from pre- to post-intervention in both group (intervention and control group). Based on previous studies on technology-based physical activity interventions in university students, mean effect sizes of around  $d = 0.5$  are expected in analyses. To detect such intervention effects in two-sided significance testing ( $\alpha = .05$ ) with a power of 80%, a sample size of 128 participants is required. Taking into account an expected study drop-out of about 20%, 150 participants must be included in the study and participants response rate of about 50%, hence, 300 students (six classes of physical education course) will be invited.

Number of Participants

N=6 physical education course lecturers

(a) n=3 will be assigned to the intervention group,

(b) n=3 will be assigned to the control group.

n=300 students will be randomised 1:1 to either an intervention arm

(a) n=150 a technology-supported physical education course (intervention group)

(b) n=150 non-technology-supported physical education course (control group).

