## 6. RESEARCH PLAN / STUDY DESIGN

### 6.1 Type of study

This is a two-arm parallel, randomised controlled trial of a technology-supported physical education course intervention for students enrolled in an elective unit of study. The six lecturers who agree to participate will be randomly assigned to the intervention or control group. Students who enrol randomly by the University system with the participated lecturers of physical education course will be invited to participate in the study. The intervention lecturers will have lecturer training and implement the 16-week technology-supported physical education course intervention for one semester. The Primary outcome is to examine the difference in students' physical activity levels, knowledge and motivation at post-test (at the completion of a 16-week semester) compared with the control group. The secondary outcome is students' experience and enjoyment of the technology-supported physical education course intervention.

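### Six lecturers are randomised, three per arm, but the 128 and its 80% power come from a formula for individually randomised, independent students

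*Protocol*

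**What the plan says.** Protocol 6.1 describes the allocation: "The six lecturers who agree to participate will be randomly assigned to the intervention or control group". Sections 6.4 and 6.6 say the same, and the list in 6.2 puts three lecturers in each arm ("a) n=3 will be assigned to the intervention group"; "b) n=3 will be assigned to the control group"). Students are invited because they are enrolled with a participating lecturer; 6.1 says the university system places them at random. No section describes a procedure for randomising students.

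Section 6.2 nevertheless says that "n=300 students will be randomised 1:1 to either an intervention arm", and the synopsis repeats it.

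The calculation in 6.2 is based on the "difference in change in the primary outcome (physical activity) from pre- to post-intervention", with d = 0.5 and two-sided alpha of 0.05. It concludes that "with a power of 80%, a sample size of 128 participants is required". It then allows for about 20% drop-out (150 to be included) and a response rate of about 50% (300 to be invited). It contains no ICC, no design effect and no allowance for there being only six lecturers.

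Section 6.3 plans linear mixed models with the pre-test as covariate, justified by missing data. It names no lecturer or class effect.

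**The concern.** The protocol contradicts itself on the unit of randomisation, and its sample size belongs to the reading that the design sections do not support. When lecturers are allocated, differences between lecturers become part of the treatment contrast, and only three lecturers per arm average them out. Random placement of students by the university could balance the classes at entry. It would not stop post-test scores from clustering after 16 weeks with one lecturer.

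The 80% is the protocol's only justification for its size. If it is taken at face value, a non-significant result would be read as evidence against an effect of 0.5 that the design could easily miss.

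**Working it through.** **Inputs.** From Protocol 6.2: d = 0.5, two-sided alpha 0.05, power 80%, N = 128, 3 + 3 lecturers, 300 students, drop-out 20%. Assumed, because the protocol gives no value: ICC from 0.01 to 0.10. Also assumed: equal numbers per lecturer, and no further gain from the pre-test covariate, since 6.2 already sizes on change.

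**1. The plan's own figure.** The normal approximation gives 2 × (1.96 + 0.84)² / 0.5² = 62.7, so 63 per arm, 126 in total. The exact two-sample t-test gives 63.77, so 64 per arm, **128** in total, with power 80.1%. The figure is reproduced, for independent students on 126 degrees of freedom.

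**2. Formulas for six lecturers.** With m = N/6 students per lecturer:

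- design effect DE = 1 + (m − 1) × ICC
- non-centrality λ = 0.5 × √(N / (4 × DE))
- power by design effect alone = Φ(λ − 1.96)
- power on a lecturer-level test: non-central t with 6 − 2 = 4 degrees of freedom, critical value 2.776

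Example, N = 128 and ICC 0.05: m = 21.3; DE = 1 + 20.3 × 0.05 = 2.02; effective N = 63; λ = 0.5 × √(63.5/4) = 1.99. Power is 51% by design effect and 33% on 4 degrees of freedom.

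**3. Power for d = 0.5.** The 240 is 300 × 0.8, that is, every invited student takes part and 20% drop out.

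| ICC | 128: design effect | 128: 4 df | 240: design effect | 240: 4 df |
|---|---|---|---|---|
| 0.01 | 73% | 50% | 91% | 69% |
| 0.02 | 67% | 44% | 83% | 59% |
| 0.05 | 51% | 33% | 62% | 41% |
| 0.10 | 37% | 24% | 42% | 27% |

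At N = 128, power by design effect alone is already 77% at ICC 0.005. On 4 degrees of freedom it is 57% even at ICC 0.

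**4. Ceiling with unlimited students per lecturer.** As m grows, λ tends to 0.5 × √(1.5/ICC).

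| ICC | λ | design effect | 4 df |
|---|---|---|---|
| 0.01 | 6.12 | above 99% | 99% |
| 0.02 | 4.33 | 99% | 89% |
| 0.05 | 2.74 | 78% | 55% |
| 0.10 | 1.94 | 49% | 32% |

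**5. Effect detectable with 80% power, N = 128.** This is λ₈₀ × √(4 × DE / N), where λ₈₀ is 2.80 by the normal approximation and 3.76 on 4 degrees of freedom. At ICC 0.01, 0.02, 0.05 and 0.10 it is 0.54, 0.59, 0.70 and 0.86 by design effect, and 0.73, 0.79, 0.94 and 1.16 on 4 degrees of freedom.

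**The case against.** **More students.** A reader might infer that enlarging the classes of the same six lecturers achieves almost nothing. The figures do not support that at small ICCs. At ICC 0.01 on 4 degrees of freedom, power is 50% with 128 analysed, 69% with 240 and 80% with 360. By design effect alone, 240 exceeds 80% at both 0.01 and 0.02. However, 6.2 reaches 300 as the number to invite and expects half to respond, so 240 is the favourable case. Section 6.5 lets a lecturer invite another class when fewer than 30 agree, which might raise enrolment by an amount that cannot be computed from the text.

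**Degrees of freedom.** A reader might also treat the 4 degrees of freedom as fixed by the design. They belong to a lecturer-level test. Section 6.3 plans mixed models, and their random effects and degrees-of-freedom method may be set in an analysis plan that is not at hand. Nor does the protocol establish that lecturer will be left out of the model. The two columns therefore stand side by side. A lecturer effect would make the test valid, but it would not restore the 80%.

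**Pre-test covariate.** If the pre-post correlation were 0.5 (an assumption), change and post-test scores would have the same standard deviation. Adjustment would then give an effective d of 0.5/√(1 − 0.25) = 0.58. At N = 128 and ICC 0.01, power would be 85% by design effect and 61% on 4 degrees of freedom; at ICC 0.02, 79% and 55%. This matters at the lower end of the range. The plan does not claim this gain.

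**Likely size of the ICC.** Random placement and identical course content in both arms (Table 1) argue against the upper end of the range. They do not imply an ICC of zero.

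**Conclusion.** The point holds. Six lecturers are randomised, the 128 is the size for independent students, and the 80% does not describe the 3-versus-3 design. With 128 analysed, power falls to between 73% and 37% over ICC 0.01 to 0.10 by design effect alone, or between 50% and 24% on 4 degrees of freedom. At ICC 0.05 or above, no class size brings six lecturers to 80% for d = 0.5 without credit for covariate adjustment.

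The size of the shortfall rests on the assumed ICC and on the degrees of freedom. Its existence at N = 128 depends little on either: a lecturer-level test misses 80% even at ICC 0, and the design effect alone misses it from ICC 0.005. Power near or above 80% needs a favourable combination, such as a small ICC with many more than 128 analysed or with a useful gain from the covariate, and 6.2 relies on none of these.

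The lecturer is taken here as the cluster. Section 6.4 asks for lecturers who run two classes but counts six classes for six lecturers, so the structure below the lecturer should be made clear. Whether 150 covers 20% drop-out is a separate question, kept out by working from 128.

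**What to change.** - Synopsis and 6.1: describe the trial as cluster-randomised with the lecturer as the unit.
- Synopsis and 6.2: delete the statement that students are randomised 1:1.
- 6.2: replace the 80% claim with power and minimum detectable effect for 3 + 3 lecturers over a stated ICC range (for example 0.01 to 0.10), for the number expected to be analysed, and name the degrees of freedom assumed.
- 6.3: include a lecturer effect in the mixed model, with small-sample degrees of freedom. Without it the intervals would be too narrow if scores cluster by lecturer.
- 6.2 or 6.3: state that the result will be read from the estimate and its confidence interval, and that a non-significant result does not rule out d = 0.5.

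The cost is wording plus one model term. No extra lecturers or students are required. The price is a less favourable stated power and wider intervals.

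### Section 6.2 allows for 20% drop-out with 150 participants where its own figures give 160, and its counts of students invited, included and randomised do not agree

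*Protocol*

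**What the plan says.** Section 6.2 of the protocol builds its sample size in one chain.

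- **Endpoint.** "The sample size calculation is based on the difference in change in the primary outcome (physical activity"), pre- to post-intervention, compared between the two groups.
- **Design values.** A standardised effect of around d = 0.5, a two-sided test at α = .05, and 80% power.
- **Requirement.** "a sample size of 128 participants is required".
- **Drop-out.** "Taking into account an expected study drop-out of about 20%, 150 participants must be included in the study".
- **Invitations.** At a response rate of about 50%, "hence, 300 students (six classes of physical education course) will be invited".

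Directly below this chain, section 6.2 lists 300 students as randomised 1:1, with 150 in each arm. The synopsis row on number of participants says the same. Section 6.4 gives six classes of 20 to 50 students each.

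**The concern.** The 128 is the number needed for analysis before any loss. The drop-out step exists to protect that number. If the inflated figure is too small for the stated drop-out, then the requirement, the drop-out, the enrolment and the power cannot all be true together. The error also carries forward, because the number invited is calculated from the number included.

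The count of 300 is a second difficulty. It appears once as the number invited, of whom about half are expected to take part, and again as the number randomised. A reader cannot tell whether the trial plans for 150 or 300 participants. This is the only sample-size justification in the protocol, and any later allowance for clustering would be built on it.

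**Working it through.** **Inputs, all from section 6.2 unless stated.** d = 0.5; two-sided α = 0.05; power 80%; 1:1 allocation; drop-out 20%; response 50%; 150 included; 300 invited; 300 randomised (also in the synopsis). Class sizes of 20 to 50 are from section 6.4.

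**1. Reproduce the plan's base figure.** A two-sample t-test (noncentral t) with these values needs 63.77 per arm. Rounded up, that is 64 per arm, or 2 × 64 = 128 in total. This matches the protocol exactly. The normal approximation gives 63 per arm, or 126.

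**2. Inflate for drop-out.** To keep N completers when a fraction f is lost, enrol N/(1 − f):

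- 128/(1 − 0.20) = 160, against the stated 150.
- The common mistake of multiplying instead gives 128 × 1.20 = 153.6, rounded up to 154. That is not 150 either.
- Starting from 126, the division gives 126/0.80 = 157.5, so 158.

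**3. Find the drop-out that 150 does cover.** 1 − 128/150 = 0.147, or 14.7%. At 15%, 150 × 0.85 = 127.5, already just below 128.

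**4. Follow the protocol's own chain.** 300 invited × 0.50 = 150 enrolled, and 150 × 0.80 = 120 completers, which is 60 per arm and 8 below the requirement.

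**5. Power at d = 0.5, individual randomisation, no baseline adjustment.**

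| Enrolled | Completers at 20% drop-out | Power (t-test) |
|---|---|---|
| 150 | 120 | 77.5% |
| 160 | 128 | 80.1% |
| 300 | 240 | 97.1% |

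The gap between the first two rows is 80.1 − 77.5 = 2.6 percentage points. By the normal approximation, power with 120 completers is 78.2%, which is 1.8 points below 80%. The effect detectable with 80% power moves from 0.499 (128 completers) to 0.516 (120 completers).

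**6. Invitations.** 160/0.50 = 320. Six classes of at most 50 hold 6 × 50 = 300, so 320 cannot be reached from six classes.

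**The case against.** Four points can be made in the plan's defence.

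**The power loss is conditional.** A reader might infer that the trial misses its 80% target. The protocol does not support that as a flat statement, because section 6.2 and the synopsis also have 300 students randomised. With 300 enrolled, unclustered power is about 97%. This objection stands, and the power claim must be tied to 150 being total enrolment. It does not rescue the inflation step, which is wrong on either reading. Nor can the 97% be taken as reassurance: the same section derives 300 as the number invited, and the figure ignores that lecturers, not individual students, are allocated (sections 6.1 and 6.4).

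**The inputs are approximate.** The drop-out, response rate and effect size are all given as rounded values, and a detectable effect of 0.516 is still around 0.5. This stands as an argument about severity. It does not make 150 the right answer to the stated 20%.

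**The planned analysis may be more efficient.** Section 6.3 uses linear mixed models with the pre-test value as covariate, whereas 77.5% is for an unadjusted t-test. The protocol gives no pre–post correlation r, so this needs an assumption. If d refers to the SD of change, adjustment multiplies the variance by (1 + r)/2, and 120 completers reach 80% power for r up to about 0.88. If d refers to the post-test SD, the factor is 1 − r², and r of about 0.25 or more is enough. At r = 0.5 power is 88% either way. So it does not follow that the planned analysis falls below 80% at the individual level. What does follow is that the stated calculation does not deliver its stated power by its own method.

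**Recruitment has a top-up.** Section 6.5 lets lecturers invite another class if fewer than 30 students agree. Whether that threshold applies per class or overall is not stated. Read per class, it would give 6 × 30 = 180, above 160. The provision may soften a shortfall, but it is not part of the calculation in section 6.2.

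**Conclusion.** The inflation step is wrong as written. From the protocol's own 128 and 20%, enrolment should be 160; 150 corresponds to 14.7% drop-out. If 150 is total enrolment, 120 students are expected to complete, and power at d = 0.5 is 77.5% instead of 80%. That figure assumes a two-sample t-test, individual randomisation and no baseline adjustment.

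Separately, 300 cannot be both the number invited at a 50% response and the number randomised. Which one is meant decides whether unclustered power is about 77.5% or about 97%.

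The arithmetic slip is a minor correction of a stated figure: 10 enrolled students and about 2.6 power points. None of these figures allows for clustering by lecturer or class, which is a separate matter, so neither 150 nor 160 by itself establishes the trial's power.

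**What to change.** Reconcile the numbers invited, enrolled or randomised, and expected to complete, so that section 6.2 and the synopsis row on number of participants agree. Then correct the inflation step in one of two ways.

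1. **Keep 150 enrolled and 300 invited.** State that 120 expected completers give about 77.5% power at d = 0.5 before any allowance for clustering by lecturer or class. The cost is a reworded paragraph and a slightly lower stated power, with no extra recruitment.
2. **State 160 enrolled and 320 invited.** This restores 128 completers and 80.1% power on the same basis. It is more than 20 extra invitations, because six classes hold at most 300 students, so at least one further class is needed. Section 6.4 requires participating lecturers to run two classes, so further classes may be available. The text should say where the extra students come from.

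If 300 students are in fact to be enrolled, the statements that 150 are included and 300 invited must change instead, and the number invited must be recalculated: 300/0.50 = 600 at the stated response rate.

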#### **6.4 Recruitment and selection of participants\***

The randomised controlled trial will include six lecturers and six classes (20 to 50 students each class or  $n=300$ ). There are two recruitment processes in this RCT including the lecturer and students. The lecturer will be included in the RCT if he/she meets the following inclusion criteria: 1) run two classes of the physical education course; 2) willing to take part in lecturer training before the physical education course class begins; and 3) willing to invite their students to take part in the pilot study. The chief investigator A/[name] will be sending the recruitment to applicable members of staff at Universitas Pendidikan Indonesia especially lecturers who run the elective physical education course.

The chief investigator A/[name] will be sending the recruitment letter to students enrolled in a physical education course via the participating lecturers (and consenting). Participation in this RCT is voluntary, and all participants will be given Participant Information Statements and invited to sign a Participant Consent Form to participate. Participation or non-participation in this study will not affect students' scores in physical education courses. The number of students in each class varies from 20-50 students. Students will be included in the RCT if they meet the following inclusion criteria: 1) students enrolled in a physical education course with a lecturer who will participate in the pilot study; 2) voluntarily participate in the RCT; and 3) owns an android smartphone. The six lecturers who agree to participate will be randomly assigned to intervention or control. Participation in this RCT is voluntary, and all lecturers and students will be given Participant Information Statements and be invited to sign a Participant Consent Form to participate.

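### The protocol gives the trial size both as 150 included out of 300 invited and as 300 randomised, and at its own rates the six-class base scheme falls short of the 128 completers it requires

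*Protocol*

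**What the plan says.** Section 6.2 builds the size in three steps for d = 0.5 and two-sided alpha of 0.05:

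- Analysed: "with a power of 80%, a sample size of 128 participants is required".
- Included: "Taking into account an expected study drop-out of about 20%, 150 participants must be included in the study".
- Invited, at a response of about 50%: "hence, 300 students (six classes of physical education course) will be invited".

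The list of participant numbers that closes the same section then states "n=300 students will be randomised 1:1 to either an intervention arm", with 150 in each arm. The synopsis gives the same 300 and 150 per arm.

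Section 6.4 states "The randomised controlled trial will include six lecturers and six classes (20 to 50 students each class or" and completes the sentence with n=300. It repeats the class-size range of 20 to 50, and says that participation is voluntary and by signed consent. Its criteria for lecturers include "1) run two classes of the physical education course". Section 6.5 adds a reserve: if fewer than 30 students agree, the course lecturer invites students from another physical education class.

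**The concern.** Two things do not fit together. First, 300 is the number invited in the derivation and the number randomised in the list beneath it. The two could coincide only if every invited student consented, yet the derivation plans for half.

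Second, 300 is the largest number that six classes of the stated size can hold, not the expected number, so the recruitment base is set at its ceiling.

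What is at stake is the meaning of full enrolment. A trial that enrols 150 could be reported as complete or as half recruited, depending on which sentence is read. An ethics committee or reader also cannot tell from the text what power the six classes are expected to give.

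**Working it through.** **Inputs.** From Section 6.2: d = 0.5, two-sided alpha 0.05, power 80%, 128 analysed, drop-out about 20%, response about 50%, 150 included, 300 invited, 300 randomised 1:1. From Section 6.4: six classes of 20 to 50 students. From Section 6.5: the reserve triggered below 30 consenting.

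**Step 1. Reproduce 128.** The normal approximation gives n per arm = 2 × (1.96 + 0.8416)² / 0.5² = 62.8, so 63 per arm and 126 in total. The exact two-sample t calculation (noncentral t) gives 64 per arm, 128 in total, with power 80.1%. The figure of 128 is correct for individually randomised students.

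**Step 2. Drop-out.** Enrolled = 128 / (1 − 0.20) = 160, not 150. Multiplying instead of dividing gives 128 × 1.2 = 153.6, which is close to 150 and may be where it came from. Going from 150 to 128 implies drop-out of 1 − 128/150 = 14.7%. At the stated 20%, 150 enrolled leave 150 × 0.8 = 120 completers, with power 77.5%.

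**Step 3. Response.** 150 / 0.5 = 300 invited, as stated. From 160 it would be 160 / 0.5 = 320. If 300 are really to be randomised, 300 / 0.5 = 600 must be invited, which is twelve classes of 50. They would leave 300 × 0.8 = 240 completers, with power 97.1%.

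**Step 4. Yield of six classes.** Completers = 6 × class size × 0.5 × 0.8.

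| Mean class size | Invited | Enrolled | Completers | Power at d = 0.5 |
|---|---|---|---|---|
| 20 | 120 | 60 | 48 | 39.6% |
| 30 | 180 | 90 | 72 | 55.3% |
| 35 | 210 | 105 | 84 | 62.0% |
| 40 | 240 | 120 | 96 | 67.9% |
| 50 | 300 | 150 | 120 | 77.5% |

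The protocol gives only the range 20 to 50. The row for 35 is its midpoint, taken here as an assumption. The mean class size needed for 128 is 128 / (6 × 0.5 × 0.8) = 53.3, above the stated maximum.

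**Step 5. The Section 6.5 reserve.** The text does not say whether fewer than 30 means per class or overall.

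- Per class: the largest class yields 50 × 0.5 = 25 consenting, below 30, so the reserve would be called at every stated class size. If each lecturer added one class of equal size, twelve classes would give 12 × 20 × 0.4 = 96 to 12 × 50 × 0.4 = 240 completers. They would reach 128 at a mean of 128 / (12 × 0.4) = 26.7, that is 27 per class.
- Overall: six classes yield 60 to 150 consenting, always above 30, so the reserve is never called and the shortfall in Step 4 stands.

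All the powers treat students as individually randomised, as Section 6.2 does.

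**The case against.** - **Labelling.** Lecturers are assigned first and then invite their students, so 300 could mean the students in allocated classes and 150 those who consent. That is a possible intention. But the list is headed as the number of participants and speaks of students randomised, while the derivation uses the same word, participants, for the 150. The reading explains the conflict without removing it, and it means the protocol's authors must say which number they meant.
- **Small gap at the ceiling.** With six full classes the yield is 120 against 128, or 77.5% power against 80%. Both rates are given as approximate, and retention of 128/150 = 85.3%, or response of 128/(300 × 0.8) = 53.3%, would close it. This stands. That part of the gap comes wholly from the drop-out step. The larger loss comes from classes below 50, which Section 6.4 itself expects.
- **The reserve class.** A reader might infer that the scheme can never reach 128. The document does not support that. On a per-class reading of Section 6.5 the reserve would be used throughout, and 128 is then reachable once classes average 27. What remains is that the trigger is ambiguous and is not linked to 128 or 150.
- **Two classes per lecturer.** A reader might also infer that six lecturers with two classes each contradict six classes. They do not: running two classes is an eligibility condition for lecturers, and nothing says both classes enter the trial. One trial class per lecturer, with the other available as a reserve, fits Sections 6.4 and 6.5 together.

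**Conclusion.** The point holds in two parts.

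The first is certain: the current text states the trial size as 150 and as 300, a factor of two, and voluntary consent at 50% response rules out both being true.

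The second is conditional: at about 50% response and 20% drop-out, the six-class base scheme gives 48 to 120 completers against the 128 required. Power is about 40% to 77.5%, and 62% if classes average the assumed midpoint of 35. It falls short unless the Section 6.5 reserve is used, and that trigger is neither defined per class or overall nor set against a target.

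These powers rest on d = 0.5 and on individual randomisation. Because the six lecturers are the units assigned, any similarity among students of the same lecturer would lower power further. So reaching 128 by adding classes under the same lecturers would not by itself show that the trial is adequately powered.

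The point should be corrected, since enrolment will be judged against these numbers.

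**What to change.** 1. Give one chain of invited, enrolled and analysed numbers, in total and per arm, and use it unchanged in the synopsis, Section 6.2 and Section 6.4. Correct whichever of 150 included and 300 randomised was not intended.
2. Correct the drop-out step: at 20%, 128 analysed needs 160 enrolled and 320 invited. Otherwise state the drop-out rate that 150 assumes (14.7%).
3. In Section 6.4, replace the equation of six classes with 300 by the range 120 to 300 and the expected class size.
4. Then either state the size and power that six classes of that expected size deliver, or define the Section 6.5 trigger against the enrolment target, saying whether it applies per class or overall, so that each lecturer's second class is invited when needed.
5. State that the power figures assume individual randomisation although lecturers are the units assigned.

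The cost is protocol wording. If second classes are invited, there are more online questionnaires to collect, but no new lecturers or sites.
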